
**Fig. 1 Fig1:**
[figure not shown]
Flowchart of study protocol from enrolment to sample acquisition and correlation of sequencing results with clinical parameters

### Data management

Patient derived metadata will be uploaded after discharging the patient to a privacy protection compliant online database (Sosci-Survey). Once uploaded it will not possible to alter the data. Only the PI from Goettingen will have access to these pseudonymized data.

### Statistical methods

Prior statistical testing, normal distribution and homogeneity of variance will be examined using, QQ-plots and Levene’s test, respectively. If the data will be considered as normally distributed and the homogeneity is not violated, t-test for two groups and ANOVA with consecutive post-hoc tukey-type multiple comparisons for data with more than two groups will be performed. Non-normally distributed variables will be compared with Wilcoxon rank test (two groups) or non-parametric multiple comparisons (Kruskal–Wallis) for more than two groups. Statistical methods will compare groups for primary and secondary outcomes. For alpha diversity the following parameters will be calculated and presented in boxplots: Shannon-Index, Chao1-Estimator and observed richness (i.e. species). For beta diversity the following distances metrics will be performed: Bray–Curtis, unweighted and weighted UniFrac distances. The beta diversity will be visualized with principal coordinate analysis plot (PCoA). Significances will be calculated using PERMANOVA and pairwise adonis test. Further investigation of a significant distance in beta diversity will be conducted with high dimensional class comparisons using linear discriminant analysis of effect size (https://huttenhower.sph.harvard.edu/lefse/). Furthermore, a microbial network will be constructed after centered log-ratio transform of the out-table and visualized with Cytoscape.

Measures of diagnostic and predictive accuracy will be calculated, including area under the curve (AUC) and optimal cut-off point for classification (using simultaneous maximization of sensitivity and specificity).

Cox regression will be performed to interrelate length of hospital stay and the microbiome patterns, which will be calculated and will be most distinctive for the study population. 30-days mortality will also be analyzed using Cox-Regression with a calculated set of microbes as regressors. Number of interventions will be analyzed using negative binomial regression with the same microbes as regressors. Whenever feasible, 95-% confidence intervals will be provided for estimates.

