### Outcomes

This prospective translational study aims to evaluate the orointestinal microbiome as a potential biomarker for the course, severity and outcome of patients with AP. From each patient one buccal and rectal swab will be collected within 72 h after hospital admission. As primary endpoint we will analyze the association between microbial composition and the revised Atlanta classification. Secondary endpoints will be the association between microbiome signatures and length of hospital stay, numbers of interventions and mortality. For these analyses, alpha and beta diversity of microbiota will be determined and compared between mild, moderately severe and severe AP. If the analysis will reveal a set of microbes whose presence or abundancies are able to distinguish among the revised Atlanta classification (differential abundances), the microbiome could be employed as early clinical biomarker to guide clinical management of AP patients (e.g. early use of antibiotics).

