### Sample size

We calculate to include 400 patients in total (300 with mild pancreatitis (Atlanta I), and 100 with moderately severe or severe AP (Atlanta II–III). This sample size was calculated before enrolment. The sample size is based on the variability of the measured area under the curve (AUC), which is calculated for assessing the predictive accuracy of outcomes. Assuming a true AUC of 0.8, a total of 100 patients per group will provide a power of 85% (99%) when testing against the alternative of an AUC > 0.7 (0.6) at one-sided 2.5% significance level. A 95%-confidence interval for an AUC of 0.8 [0.735; 0.855] will have a total width of 0.12.

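### The AUC test is powered as for a marker fixed in advance, but the microbial marker is to be found in the same 400 patients, and no internal validation is named

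*Protocol article*

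**What the plan says.** Under Sample size, the article plans a single cohort: "We calculate to include 400 patients in total (300 with mild pancreatitis (Atlanta I), and 100 with moderately severe or severe AP". It gives the basis as follows: "The sample size is based on the variability of the measured area under the curve (AUC". With a true AUC of 0.8 and 100 per group, power is put at 85% (99%), "when testing against the alternative of an AUC > 0.7 (0.6) at one-sided 2.5% significance level". The precision statement reads: "A 95%-confidence interval for an AUC of 0.8 [0.735; 0.855] will have a total width of 0.12".

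The marker is not named in advance. Under Outcomes, the hope is that the analysis will find "a set of microbes whose presence or abundancies are able to distinguish among the revised Atlanta classification". Under Statistical methods, a significant beta-diversity distance is followed up by a high-dimensional class comparison (LEfSe). The accuracy measures come next, "including area under the curve (AUC) and optimal cut-off point for classification (using simultaneous maximization of sensitivity and specificity".

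The same section enters "microbiome patterns, which will be calculated and will be most distinctive for the study population" into a Cox model for length of stay. It then uses a calculated set of microbes in the models for 30-day mortality and number of interventions. The article mentions no second cohort, hold-out, resampling or optimism correction.

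**The concern.** Power and interval formulas for an AUC account for sampling error of a score that was settled beforehand. Here the score is to be built by looking for taxa that separate the severity classes in the cohort being analysed. If the AUC is then calculated in those patients, it also contains selection and fitting optimism, which the sample-size statement does not cover. A cut-off chosen to maximise sensitivity and specificity in the same data adds to this.

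At stake are the reported accuracy and the comparison with 0.7. A signature with little or no predictive value could appear close to the AUC of 0.8 for which the study was sized. The article links a positive finding, conditionally, to early clinical management, so an inflated AUC would matter to readers.

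**Working it through.** **1. The plan's own figures.** The inputs are from Sample size: AUC 0.8 against 0.7, 100 v 100, one-sided 2.5%. The Hanley-McNeil variance is

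Var(A) = [A(1−A) + (n1−1)(Q1−A²) + (n0−1)(Q2−A²)] / (n1·n0), with Q1 = A/(2−A) and Q2 = 2A²/(1+A).

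- A = 0.8: Q1 = 0.6667, Q2 = 0.7111. Var = (0.16 + 99×0.02667 + 99×0.07111)/10,000 = 0.000984, so SE = 0.0314.
- A = 0.7: Q1 = 0.5385, Q2 = 0.5765. Var = (0.21 + 99×0.04846 + 99×0.08647)/10,000 = 0.001357, so SE = 0.0368.
- Power on the logit scale: the difference is 1.3863 − 0.8473 = 0.5390; the SEs are 0.0368/0.21 = 0.175 (null) and 0.0314/0.16 = 0.196 (alternative). (0.5390 − 1.96×0.175)/0.196 ≈ 1.0, so power is 84%. Wald versions give 81% and 89%. The stated 85% is reproduced.
- 95% interval: 0.739 to 0.861 (Wald, width 0.123) or 0.731 to 0.855 (logit). The stated 0.735 to 0.855 is reproduced.

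The arithmetic is therefore sound. The formula has no term for choosing or fitting the marker.

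**2. What it takes to pass 0.7.** With 100 v 300 and an apparent AUC of 0.76: Q1 = 0.6129, Q2 = 0.6564, Var = (0.1824 + 99×0.0353 + 299×0.0788)/30,000 = 0.000908, SE = 0.0301. The lower limit is 0.76 − 1.96×0.0301 = 0.701. An apparent AUC of about 0.76 is thus enough.

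**3. What selection alone produces.** Taxa unrelated to severity were simulated for 100 v 300 patients and screened one at a time. The best were combined in a linear score, and the AUC was taken in the same 400 patients. The numbers of candidates and of taxa kept are assumptions, because the article gives neither. A correctly working test would pass 0.7 in at most 2.5% of runs.

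| Kept of candidates (assumed) | Mean apparent AUC, independent taxa | Lower 95% limit above 0.7 | Correlated, zero-inflated taxa: AUC; limit above 0.7 |
|---|---|---|---|
| 5 of 20 | 0.62 | about 0% | not run |
| 10 of 100 | 0.70 | about 2% | 0.69; 0% |
| 10 of 500 | 0.75 | 33–58% | 0.74; 10% |
| 20 of 200 | 0.78 | 95–97% | 0.75; 29% |
| 20 of 500 | 0.82 | 100% | 0.79; 98% |

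The range for 10 of 500 reflects repeats that differed in detail. A single best taxon gives only 0.57–0.61, even from 1000 candidates. For 20 of 500 independent taxa, the optimised cut-off shows a mean sensitivity and specificity of 0.76 each, although the marker is useless.

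**4. The same noise, validated.** With selection and fitting redone inside each fold of 10-fold cross-validation, the mean AUC returns to about 0.50–0.52. A 50:50 split also gives about 0.50, but it leaves 50 v 150 for the test. There the SEs are 0.0401 (A = 0.8) and 0.0454 (A = 0.7). Power against 0.7 is Φ(0.1/0.0401 − 1.96) = 70% with the alternative SE, Φ((0.1 − 1.96×0.0454)/0.0401) = 61% with both SEs, and 68% on the logit scale. The interval width rises to 0.157.

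**The case against.** The strongest reply is that a condensed article may leave the resampling scheme to an analysis plan that is not shown. That is fair. No sentence says that the AUC is calculated in the patients used for selection; this is inferred from the single cohort and the absence of any other data. What remains is visible in the article itself: its power statement treats the marker as fixed, while its Outcomes and Statistical methods sections describe one derived from the data.

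Four stronger readings are tempting but not supported.

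- *The plan searches hundreds of taxa.* The article gives no count. Species-level sequencing of two body sites by two methods makes large numbers plausible, but with few candidates or a single taxon the effect is too small to pass 0.7. An AUC for one diversity index would carry little selection optimism.
- *The false-positive rate is 100%.* LEfSe is reserved for a significant beta-diversity distance, and the simulations do not include that gate. Under a global null, at an assumed 5% per test, three distance metrics would open it in at most 3×5% = 15% of cases per dataset. With two sites and two sequencing methods the bound is 4×15% = 60%. The AUC step is not expressly tied to this gate, so how far the gate protects is unknown.
- *The secondary models reuse the severity-selected microbes.* The text does not say that these sets are chosen on the Atlanta class.
- *The primary endpoint is compromised.* It is an association, and its PERMANOVA test is not touched by AUC optimism. Clinical use is also worded as a possibility, not as a decision rule.

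**Conclusion.** The concern holds in a bounded form. The 85% power and the interval are arithmetically right but apply to a marker fixed in advance, which is not what the study describes. If accuracy is calculated in the selection cohort, it is biased upwards by an amount that the article does not allow a reader to fix. Under pure noise and independent taxa, this runs from negligible passing of 0.7 (5 of 20, 10 of 100) to near-certain passing (20 of 200, 20 of 500). Correlation and zero inflation reduce it, sharply in the middle of the range. These rates rest on assumed taxon counts, on univariate screening with a linear score, and on no beta-diversity gate. They describe the AUC, the cut-off and the test against 0.7 only.

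**What to change.** State in the protocol or analysis plan that:

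- taxon selection, score fitting and cut-off choice are all repeated inside cross-validation, or inside a bootstrap optimism correction;
- the test against 0.7 and the reported AUC, sensitivity and specificity use only the internally validated values;
- the power statement under Sample size assumes a fixed marker;
- if microbes selected on severity are used in the length-of-stay, intervention and mortality models, the out-of-fold score is entered there, or those results are labelled as not independent of the severity finding.

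The choice of resampling scheme is open. Locking the signature and cut-off and testing them in new patients would also serve, with the power restated. A 50:50 split of the 400 is not advised, because power against 0.7 falls to about 60–70%. The cost is some wording, computing time and a lower reported AUC; all 400 patients stay in the analysis.

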## Abstract

**Background:**

Acute pancreatitis (AP) is an inflammatory disorder that causes a considerable economic health burden. While the overall mortality is low, around 20% of patients have a complicated course of disease resulting in increased morbidity and mortality. There is an emerging body of evidence that the microbiome exerts a crucial impact on the pathophysiology and course of AP. For several decades multiple clinical and laboratory parameters have been evaluated, and complex scoring systems were developed to predict the clinical course of AP upon admission. However, the majority of scoring systems are determined after several days and achieve a sensitivity around 70% for early prediction of severe AP. Thus, continued efforts are required to investigate reliable biomarkers for the early prediction of severity in order to guide early clinical management of AP patients.

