## Background

Acute pancreatitis (AP) is an inflammatory disorder that causes a considerable economic health burden [1]. While the majority of AP show a mild clinical course, about 20% of patients suffer from moderate or severe disease with major local and systemic complications and a prolonged hospital stay [2, 3]. Furthermore, severe pancreatitis is associated with a dramatic increase of mortality ranging between 36 and 50% [4–6]. The revised Atlanta classification is a feasible scoring system to distinguish between mild, moderately severe and severe pancreatitis [3]. However, the revised Atlanta classification is determined in retrospect and does not guide early clinical management and risk assessment. For several decades multiple clinical and laboratory parameters have been evaluated, and complex scoring systems were developed to predict the clinical course of AP upon admission. However, scoring systems such as the *Ranson score*, *Acute Physiology and Chronic Health Evaluation II score* (APACHE II), *Bedside Index for severity in acute pancreatitis* (BISAP), *Harmless acute pancreatitis score* (HAPS), *Pancreatitis Activity Scoring System* (PASS) and the *Baltharzar-Score* mostly achieved a sensitivity around 70% for early prediction of severe AP [7–12]. Thus, continued efforts are required to investigate reliable biomarkers for the prediction of severity in order to guide early clinical management of AP patients.

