### Eligibility criteria

Patients with AP (2 out of 3 following diagnostic criteria: lipase > 3 × of upper limit (> 280U/l), abdominal pain, and imaging modalities (computed tomography (CT), magnetic resonance imaging (MRI) or ultrasound)) indicating AP will be included within 72 h after hospital admission. In our study, amylase elevation will not considered as a diagnostic criterion. In most cases, the first two criteria lead to the diagnosis of AP. Only in rare cases one of the above-mentioned imaging tools will aid to diagnose AP. Typical ultrasound features are: increased volume (> 2.4 cm in pancreas-body diameter), decreased echogenicity and peripancreatic fluid collection [22]. CT and the MRI indicate AP if parenchymal enlargement (diffuse or localized), alterations in density, diffuse margins, acute peripancreatic fluid collection and/or surrounding fat stranding are reported [23]. All recruited patients will sign the informed consent form before buccal and rectal swab collection. Pregnant women, patients < 18 years and patients who are incapable of giving consent will be excluded. The last-mentioned group includes patients who are not authorized to give consent due to psychological or other diseases. Patients who show signs of chronic pancreatitis (CP) on imaging will also be excluded.

The intake of antibiotic and probiotic medication will be recorded before the collection of the swabs and will not be considered as exclusion criteria. Patients will be categorized in 5 groups according to the time of antibiotic medication: current, within the last week, more than 1 week and less than 6 month ago, and more than 6 months ago. Together with other drugs and reported diseases the anti- and probiotic intake will be statistically associated with the orointestinal microbiome patterns and thus treated as potential confounder. Table 1 summarizes medical history and previous medication that is recorded for each patient.

**Table 1 Tab1:** Medical history and previous medication

Medical history	Previous medication
Cardiovascular diseases (e.g. coronary artery disease, peripheral artery disease, TIA, apoplex)	Metformin
Heart failure	Insulin
Diabetes mellitus	Other antidiabetics
Inflammatory bowel disease	PROTON-pump inhibitors (including occational intake)
Irritable stomach and/or bowel disease	Immune suppressors (including topical immune suppressors affecting intestinal tract)
Clostrioides difficile infection within last year	Antidepressants

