### Participant timeline

Within 72 h after hospital admission, one buccal and rectal swab will be collected for analysis of the microbiome. Patients will be followed up until their discharge and categorization into mild, moderately severe and severe AP will be performed at the day of discharge.

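### The Cox model for length of stay does not separate discharge alive from in-hospital death, so its hazard ratio cannot by itself be read as length of stay

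*Protocol article*

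**What the plan says.** All references are to the protocol article.

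- **Outcomes:** "Secondary endpoints will be the association between microbiome signatures and length of hospital stay, numbers of interventions and mortality". Length of stay is the first of these to be named.
- **Statistical methods:** "Cox regression will be performed to interrelate length of hospital stay and the microbiome patterns". A separate model is named for death: "30-days mortality will also be analyzed using Cox-Regression with a calculated set of microbes as regressors". The text does not link the two models.
- **Participant timeline:** "Patients will be followed up until their discharge". Severity grading is set for the day of discharge, and under Data management the metadata are uploaded after discharge.
- **Background:** "severe pancreatitis is associated with a dramatic increase of mortality ranging between 36 and 50" per cent. The abstract adds: "While the overall mortality is low, around 20% of patients have a complicated course of disease".
- **Sample size:** the plan is for "300 with mild pancreatitis (Atlanta I), and 100 with moderately severe or severe AP". The number of severe cases alone is not given.
- **Eligibility criteria:** "patients who are incapable of giving consent will be excluded".

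No section says what the event in the length-of-stay model is, or whether an in-hospital death is an event, a censored observation or a competing event.

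**The concern.** A hospital stay ends in one of two opposite ways, discharge alive or death. A Cox model with one event type has to put death somewhere, and neither simple choice gives a hazard ratio that can be read as length of stay.

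- **Death counted as the end of stay.** A patient who dies on day 5 contributes the same event time as a patient who goes home well on day 5. The worst outcome is scored as a short stay.
- **Death censored.** The model then estimates the rate of discharge among patients still alive in hospital. That is a legitimate cause-specific hazard. However, how long patients occupy a bed, and how many leave alive, also depends on the hazard of death, so this hazard ratio alone does not describe length of stay.

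The deaths fall mainly among severe cases, the group the microbiome marker is meant to identify. A pattern that marks a fatal course could therefore show a weak association with stay, or one in the wrong direction. The length-of-stay and mortality results could then seem to disagree for reasons of coding alone.

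**Working it through.** The article gives no power, effect size or event count for length of stay, so there is no stated figure to reproduce. The check has three steps.

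**1. How many deaths?** Deaths = number of severe cases × mortality in severe cases. The mortality range (36-50%) is from the Background. The number severe is an assumption, because Sample size pools moderately severe and severe (100 together).

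| Severe (assumed) | Deaths at 36% | Deaths at 50% | Share of 400 |
|---|---|---|---|
| 20 | 20 × 0.36 = 7.2 | 20 × 0.50 = 10 | 1.8-2.5% |
| 30 | 10.8 | 15 | 2.7-3.8% |
| 40 | 14.4 | 20 | 3.6-5.0% |
| 50 | 18 | 25 | 4.5-6.3% |

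Deaths are a small share of the cohort, but at these rates a large share of the severe cases.

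**2. What does the coding of death do to the hazard ratio?** The check used a large-sample simulation with 300 mild and 100 moderately severe or severe per 400, of whom 30 or 50 were severe, and 36% or 50% of severe cases dying. The following inputs are assumptions that are not in the article: lognormal stays with medians 6, 14 and 28 days by severity class; median time to death 5, 10 or 20 days; a binary marker carried by 80% of patients who die and 20% of all others, unrelated to the stay of survivors within each class. The Cox hazard ratio for leaving hospital, marker present versus absent, was fitted three ways. In the third, patients who die stay in the risk set as never discharged alive, which is the Fine-Gray risk set when there is no other censoring. Values below 1 mean slower or less frequent discharge.

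| Set | Median time to death | Death = event | Death censored | Death competing |
|---|---|---|---|---|
| Severe only | 5 days | 2.09-2.83 | 0.98-1.08 | 0.13-0.22 |
| Severe only | 10 days | 1.88-2.56 | 0.68-1.06 | 0.13-0.20 |
| Severe only | 20 days | 1.22-1.44 | 0.38-0.47 | 0.15-0.21 |
| All patients | 5 days | 1.05-1.16 | 0.89-1.00 | 0.56-0.70 |
| All patients | 10 days | 0.93-0.97 | 0.75-0.86 | 0.52-0.69 |
| All patients | 20 days | 0.78-0.89 | 0.64-0.82 | 0.54-0.73 |

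Within severe cases, counting death as the event makes the fatal-course marker look like a marker of shorter stay in every setting. Censoring death gives a value near 1 when deaths are early and clearly below 1 when they are late. Across all patients the value exceeds 1 only when deaths come as early as the typical mild discharge.

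**3. How far does this depend on the marker and on the mortality?** With a continuous marker (assumed +1.5 SD in patients who die, +0.5 SD in severe survivors; 20 or 40 severe; median stays 6, 14 and 30 days; median time to death 5 or 10 days), the whole-cohort hazard ratios per unit of the marker were:

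| Mortality in severe | Death = event | Death censored | Death competing |
|---|---|---|---|
| 36-50% | 0.93-0.98 | 0.87-0.94 | 0.80-0.89 |
| 20% | 0.91-0.96 | 0.89-0.95 | 0.85-0.91 |

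At 20% mortality the gap narrows but remains. For a marker that only separates Atlanta I from II-III, the hazard ratio was 0.74-0.77 with death as the event and 0.71-0.74 with death as a competing event, so the coding hardly matters.

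**The case against.** **This is silence that an analysis plan may fill.** The article names a model family for a secondary endpoint, and Cox regression includes a cause-specific Cox model. It does not say that death counts as the end of stay, and it does not say that death is censored. This stands in part: no particular miscoding can be attributed to the sponsor. But the article does fix the model, and under either simple coding the resulting hazard ratio does not by itself answer the question about length of stay.

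**The mortality premise is weaker than it looks.** A reader might infer that over a third of the severe cases in this trial will die in hospital. The document does not support that. The 36-50% is a background range not labelled in-hospital, overall mortality is described as low, and excluding patients who cannot consent may remove some of the sickest. This stands.

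**A fatal-course marker would not simply be missed.** The separate 30-day mortality model tests it directly. This stands too, so the issue is how the length-of-stay result can be read, not whether the trial can detect a marker of death.

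**The simulated marker was chosen to show the effect.** True, and for the trial's own Atlanta I versus II-III split the effect is small. In simulations with the continuous marker, the power to link it to the outcome was 5-35% with death as the event and 79-100% with death as a competing event. A reader might take this as a gain in power. It is not like for like: the second analysis targets discharge alive, and much of its signal is the deaths themselves.

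**Fine-Gray does not give length of stay either.** Correct. Its hazard ratio mixes discharge rate and mortality, so it serves as a complement to the cause-specific hazards and need not be the main analysis.

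A reader might also infer from the discharge-only wording on follow-up and upload that patients who die are not graded or recorded. Condensed timing statements do not show that.

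**Conclusion.** The concern holds in a limited form. The length-of-stay model is fixed as a Cox regression without separating discharge alive from in-hospital death, and under either simple coding its hazard ratio cannot alone be read as length of stay.

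The distortion is concentrated in severe cases. For an assumed fatal-course marker it moves the hazard ratio there from 0.13-0.22 (competing event) to 1.22-2.83 (death as event). In the whole cohort it is modest: with the continuous marker, 0.93-0.98 against 0.80-0.89. For a marker that only separates mild from more severe disease it is small.

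These sizes rest on assumed numbers of severe cases, stays, times to death and marker strengths, and on a background mortality that may be too high for the enrolled patients. The direction within severe cases is firmer than any of the values. The point concerns a secondary endpoint only and leaves the primary Atlanta analysis untouched. It is worth correcting because the correction is cheap.

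**What to change.** Replace the length-of-stay sentence under Statistical methods with wording such as: *Time from admission to discharge alive will be analysed with in-hospital death as a competing event. Cause-specific hazard ratios for discharge alive and for in-hospital death will be reported together, with a Fine-Gray model for discharge alive as a complement, and read alongside the 30-day mortality model.*

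With perhaps 7 to 25 deaths (step 1 of the working), the hazard ratio for in-hospital death will be imprecise, and the report should say so.

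The cost is one sentence and one or two extra models. No new data are needed, because the time of leaving hospital and vital status are already required for the stay and mortality endpoints.

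### The factors the plan calls potential confounders do not reappear in the alpha-diversity tests or the outcome models it specifies

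*Protocol article*

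**What the plan says.** Under Eligibility criteria, patients exposed to antibiotics or probiotics stay in the study. Their exposure, with other drugs and diseases, "will be statistically associated with the orointestinal microbiome patterns and thus treated as potential confounder". No further handling step is given.

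Statistical methods then sets out the analyses without returning to these factors:

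- **Group comparisons, including alpha diversity, if normal:** "t-test for two groups and ANOVA with consecutive post-hoc tukey-type multiple comparisons".
- **Group comparisons otherwise:** "Non-normally distributed variables will be compared with Wilcoxon rank test (two groups) or non-parametric multiple comparisons (Kruskal–Wallis) for more than two groups".
- **Beta diversity:** "Significances will be calculated using PERMANOVA and pairwise adonis test".
- **Length of stay:** "Cox regression will be performed to interrelate length of hospital stay and the microbiome patterns".
- **Mortality:** "30-days mortality will also be analyzed using Cox-Regression with a calculated set of microbes as regressors".
- **Interventions:** "Number of interventions will be analyzed using negative binomial regression with the same microbes as regressors".

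Under Outcomes, the association of microbial composition with the revised Atlanta class is primary, and alpha and beta diversity are to be compared across the three severity classes.

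**The concern.** A confounder of a severity-diversity or microbe-outcome association has two links, one to the microbiome and one to severity or outcome. The stated step examines only the first. Even a full account of both links leaves the association unadjusted unless the factor enters the model, or the analysis is stratified or restricted. The article names the factors and then specifies analyses in which they do not appear, so the two sections do not meet.

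A drug or disease that is commoner in the sicker patients and alters the flora can then produce a significant diversity difference between Atlanta classes, or a microbe-outcome association, with no contribution from the microbiome itself. Unequal exposure is plausible here: swabs may be taken up to 72 h after admission, and current antibiotic use is one of the recorded categories.

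**Working it through.** **1. What each analysis can carry, and what is written**

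| Analysis | Can take covariates? | Covariates named |
|---|---|---|
| t-test, Wilcoxon, Kruskal-Wallis | No | None |
| ANOVA with Tukey-type comparisons | Not as specified (group factor only) | None |
| Cox, 30-day mortality | Yes | Microbes are the only regressors named |
| Negative binomial, interventions | Yes | Microbes are the only regressors named |
| Cox, length of stay | Yes | Microbiome patterns; no regressor list |
| PERMANOVA / adonis | Yes | Silent |

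**2. The plan's own figure.** The only power statement (Sample size) concerns the AUC: 85% against 0.7 with 100 per group, one-sided 2.5%. With the Hanley-McNeil variance, SE(0.8) = 0.0314 and SE(0.7) = 0.0368. On the logit scale these are 0.0314/0.16 = 0.196 and 0.0368/0.21 = 0.175. Then (1.386 − 0.847 − 1.96 × 0.175)/0.196 ≈ 1.0, a power of 84%. Other variance choices give 70% to 89%. The figure is reproducible and does not bear on this point.

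**3. Size of the effect on an unadjusted test.** Inputs: 300 mild v 100 moderately severe or severe (Sample size). Assumed, because the documents give no figures: one binary exposure that lowers diversity by d SD, exposed proportions p_S (severe group) and p_M (mild group), and no true severity effect.

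- Spurious shift = d × (p_S − p_M)
- Variance in each group = 1 + d²p(1 − p)
- SE = √(Var_M/300 + Var_S/100)
- Two-sided 5% rejection ≈ Φ(shift/SE − 1.96) + Φ(−shift/SE − 1.96)

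Example, 40% v 15% and d = 0.5: shift = 0.5 × 0.25 = 0.125; Var_M = 1 + 0.25 × 0.1275 = 1.032; Var_S = 1 + 0.25 × 0.24 = 1.06; SE = √(0.00344 + 0.0106) = 0.1185; ratio 1.055; rejection about 18%.

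| Exposed, severe v mild | d (SD) | Shift / SE | By formula | Simulated Wilcoxon |
|---|---|---|---|---|
| 15% v 15% | 0.5, 1.0 | 0 | 5% | 5%, 4% |
| 30% v 15% | 0.5 | 0.075 / 0.118 | 10% | 8–9% |
| 30% v 15% | 1.0 | 0.150 / 0.126 | 22% | 20–22% |
| 40% v 15% | 0.5 | 0.125 / 0.118 | 18% | 17–18% |
| 40% v 15% | 1.0 | 0.250 / 0.127 | 50% | 48–49% |
| 50% v 20% | 0.5 | 0.150 / 0.119 | 24% | 23–24% |
| 50% v 20% | 1.0 | 0.300 / 0.128 | 65% | 65% |

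The simulations used 1,000 to 4,000 trials per scenario. A more extreme 50% v 15% at 1.0 SD gave 78%. A linear model with the exposure as covariate rejected in about 4% to 6% throughout (4.9% to 5.2% in the 4,000-trial runs).

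**4. How much adjustment the data can hold.** Table 1 lists 20 history and 14 medication items, 34 in all. The 100 moderately severe or severe patients give 100/34 ≈ 2.9 per item before any microbe enters, so adjusting for everything is not workable. The expected number of deaths is not given, so the capacity of the mortality model cannot be computed.

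**The case against.** Several counter-arguments have force.

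- **Scope.** A reader might infer that confounding stays in every microbe-outcome result. The documents do not support that. Composition, the primary endpoint, is tested largely through PERMANOVA, which can take covariates; the text neither lists nor excludes them.
- **Capability.** A reader might also infer that none of the named methods could adjust. That holds for the alpha-diversity tests as specified. Cox and negative binomial models take covariates routinely, and the article does not say that microbes are the exclusive regressors.
- **Condensed article.** Which covariates enter which model is commonly left to an analysis plan, and the factors are called only potential confounders. This excuses the absence of a list. It does not excuse naming tests that cannot use one, or naming regressors for two models without the declared factors.
- **Prediction, not causation.** The study seeks an early predictor and is sized on an AUC. An association carried partly by medication does not bias discrimination; it raises the question of added value and transportability. This stands for the AUC. It does not cover the association tests, which Outcomes makes primary.
- **Magnitude.** Every exposure rate and effect is assumed. The simulation is a two-group Wilcoxon test, whereas the plan compares three classes, and it says nothing numerical about the regressions. With balanced exposure there is no inflation.

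**Conclusion.** The point holds for the alpha-diversity tests, which carry no covariates as specified, and for the mortality and intervention models, whose only named regressors are microbes; for length of stay it is implied. For PERMANOVA the finding is silence, not exclusion. The stated association step does not supply the control that the word confounder promises.

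Under the assumed imbalances, the false-positive rate of an unadjusted two-group test runs from about 8% to 65% against a nominal 5%, and adjustment restores about 5%. These figures illustrate the mechanism and do not forecast this trial. They do not show that the results will be confounded, and they do not extend to the AUC as bias.

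**What to change.** - **Alpha diversity.** Replace the listed tests with a linear model (rank-transformed if needed) of Atlanta class plus a short prespecified covariate list from recorded items, for example pre-admission antibiotic exposure, proton-pump inhibitor use, diabetes and alcohol use disorder. Add age and sex if collected; neither is in Table 1.
- **PERMANOVA.** Enter the same list and test Atlanta class marginally.
- **Length of stay and interventions.** Add the list to the microbe terms.
- **Mortality.** Use one microbiome score with very few covariates, penalised.
- **Antibiotics.** Keep exposure before admission separate from antibiotics started afterwards. The latter may result from severity, and adjusting for them could remove real signal. Add a sensitivity analysis without current users. Eligibility criteria announces five antibiotic-timing groups but lists four; reconcile these before the variable is used.
- **AUC.** Report added value over these factors.
- **Reporting.** Show unadjusted results beside the adjusted ones.

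The cost is a small loss of degrees of freedom and some extra analysis; the Table 1 items are already recorded. If the form does not capture whether a current course began before admission, a field is needed. That should be settled early, because Data management says uploaded entries cannot be altered.
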